## Introduction

### Background

The perinatal period is a complex and vulnerable period covering the prenatal and postnatal period, which presents a series of challenges for women and men who are on their journey toward parenthood (Parfitt and Ayers, 2014). This transition can be a happy phase of life, full of positive expectations for the parents-to-be; however, it can also be a source of distress and difficulties. Indeed, it is common for pregnant women and new mothers to experience variations in mood and emotional changes due to a combination of hormonal factors and the burden of maternal responsibilities. Typically, this situation tends to resolve itself naturally, however, where there is a wide gap between expectations or resources and the reality of motherhood, psychological difficulties or mental health disorders can be consolidated or even worsen (Sipsma et al., 2016). Moreover, this situation has consequences on a larger scale because, during the perinatal period, the wellbeing and mental health of the mother, father and baby are closely interrelated (Yeaton-Massey and Herrero, 2019). Indeed, parental perinatal complications can interfere with the parent-child relationship, with the risk of significant consequences over the years (Cirulli et al., 2003; Milgrom et al., 2006; Meneghetti, 2007, 2011; Branchi et al., 2013; Stefana and Lavelli, 2017) for the child’s cognitive, social and emotional development (Kim-Cohen et al., 2005). With regards to the child, it must be taken into account that perinatal clinical psychology studies ([name] et al., 2007; [name] and [name], 2015a, b) and neuroscience research ([name] and [name], 2017) show that the mother–baby–father relationships influence the construction of the child’s neuropsychic structure in his brain, especially during the perinatal period (considered in our study to be the first 1000 days of life: from conception to 18 months of age) and, to an extent, throughout life ([name], 2006; [name] and [name], 2018).

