### Hypotheses

(1)On the basis of the current literature (Underwood et al., 2016; Okagbue et al., 2017; Hahn-Holbrook et al., 2018), we expect to find a prevalence of perinatal depression within the range of 13–18%, with higher rates during pregnancy than in the first year following childbirth.(2)Based on previous research (Ghaedrahmati et al., 2017; Leach et al., 2017), we assume that the factors associated with a higher risk of perinatal depression and anxiety will include previous history of depression and anxiety, a negative attitude toward a recent previous pregnancy, high-risk pregnancy, young maternal age, limited social support, and financial problems.(3)In accordance with previous studies on screening for antenatal or postnatal depression (Yawn et al., 2009; Zhong et al., 2014; Santos et al., 2016), we expect that both the Edinburgh Postnatal Depression Scale and the Patient Health Questionnaire-9 will be reliable and valid scales for the assessment of perinatal depression.(4)Based on a prior Italian study (Mirabella et al., 2016) showing the effectiveness of Jeannette Milgrom’s (Milgrom et al., 1999) psychological intervention among women suffering from postpartum depression, we assume that intervention can be effective also with antepartum depressed women.(5)Given that the literature (Erickson et al., 2017) has offered ambiguous results on the association between prenatal maternal mental health and the development of infant temperament, we have no specific assumptions to this regard.

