## Methods and Analysis

### Study Design

This is a prospective cohort study which merges an observational design and a pre–post intervention design. The study involves a one-year recruitment period and a one-year follow up period. The methodological strategy includes: self-report questionnaires on maternal depression, anxiety, health status, quality of life, and psychosocial risks; a self-report questionnaire to measure the infant’s temperament; a clinical interview; a structured diagnostic interview; and a psychological intervention.

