### Sample Size

Assuming 10–15% prevalence of perinatal depression as measured by EPDS (Gavin et al., 2005; Melville et al., 2010) the minimum number needed of mothers to be screened is 500.

With regard to the clinical trial on the psychological interventions for perinatal depression and anxiety, the power calculation was based on detecting an effect size of medium magnitude (*d* = 0.55) at the follow-ups on the EPDS among the patients (Cohen, 1988). We calculated that a sample size of 45 patients would result in a power of 0.95 with alpha set at 0.05. To protect against an anticipated loss to follow-up of about 30% (Mirabella et al., 2016), we planned to enroll 65 patients.

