### Data Analysis Plan

The prevalence of antenatal and postpartum depression and the risk of anxiety will be calculated and compared. Since previous studies have ascertained a higher risk of developing depression in the postpartum period, the antenatal period will be taken as a reference to calculate the odds ratio as a measure of the relative risk of depression between antenatal and postpartum periods, using chi-square as a test for statistical significance.

The sensitivity, specificity and predictive values of the EPDS and the PHQ-9 versus the MINI will be analyzed. Factors associated with ante- and post-partum depression and anxiety risk will be analyzed using a logistic regression model.

With regard to the effectiveness of treatment, standard descriptive statistics will be calculated for all questionnaires. Analysis of variance for repeated measurements will be performed to compare the differences between each initial score obtained with the different administered questionnaires and the scores at T1 (end of treatment), T2 (after 6 months) and T3 (after 12 months) will be evaluated. Bonferroni *post hoc* comparisons will be conducted. Treatment effect will be calculated using Cohen’s d for each of the follow-up times. The Reliable Change Index will be calculated for each time, in order to determine any significant clinical changes occurring in each individual case post treatment.

Data will be analyzed using the Statistical Package for Social Science (SPSS) for Windows version 22.0.

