### Strengths and Limitations of This Study

This study presents some strengths and limitations that should be mentioned. The main strengths are: (a) this study provides a new knowledge about the prevalence of perinatal depression and anxiety during both the trimesters of pregnancy and the first four trimesters after birth; (b) the large sample size is based on eleven recruitment centers located throughout Italy, and then it is representative of the pregnant population in Italy; and (c) all mothers were assessed for depression and anxiety through both self-report questionnaires and clinical interviews. The main limitation of the study is that it cannot monitor the timing and patterns of onset, duration, remission and recurrence of anxiety and depression during the entire perinatal period. Another limitation is that this protocol is the absence of a control group or waiting list condition.

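### For women enrolled in pregnancy, the uncontrolled pre-post d labelled a treatment effect cannot be separated from the move from pregnancy to the postnatal period, and no split by period of enrolment is described

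*Protocol article*

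**What the plan says.** The Study Design section describes a cohort study that "merges an observational design and a pre–post intervention design". Under Selection Criteria a woman may enter while pregnant, with no limit on gestation, or with a newborn up to six months old.

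Objective 4 is to evaluate the effectiveness of the intervention in antenatal as well as postnatal depression. Hypothesis 4 takes postpartum effectiveness from an earlier Italian study and adds the new element: "we assume that intervention can be effective also with antepartum depressed women".

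The Data Analysis Plan compares the initial scores with those at T1 (end of treatment), T2 (6 months) and T3 (12 months) by repeated-measures analysis of variance with Bonferroni post hoc comparisons. It then states: "Treatment effect will be calculated using Cohen’s d for each of the follow-up times". The Procedures section counts follow-up from the end of the intervention.

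On depression before and after birth, hypothesis 1 expects prevalence of 13–18%, "with higher rates during pregnancy than in the first year following childbirth". The Data Analysis Plan opens with the opposite premise: it cites earlier studies as showing a higher risk of developing depression postpartum, and takes the antenatal period as the reference for that reason.

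Strengths and Limitations acknowledges "the absence of a control group or waiting list condition".

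**The concern.** With one group, d measures change from any cause. For women enrolled postnatally, baseline and follow-up at least lie in the same broad period. For women enrolled in pregnancy, birth falls between baseline and most or all of the follow-ups. Anything that birth and the months after it do to depressive symptoms enters d and is reported under the name of a treatment effect.

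This matters most for the part of objective 4 that is new. If symptoms tend to ease after birth, an ineffective intervention could look effective, and the 6- and 12-month values could be read as lasting benefit. If they tend to worsen, a real benefit could be masked. Pooling antenatal and postnatal entrants hides the problem without removing it.

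The issue is distinct from regression to the mean: it would remain with a perfectly measured baseline.

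**Working it through.** **The plan's own figure.** The Sample Size section bases power on "detecting an effect size of medium magnitude (*d* = 0.55) at the follow-ups on the EPDS among the patients", with 45 patients, power 0.95 and alpha 0.05 (sidedness not stated). For a paired t test on within-woman change, power is P(|T| > t(1−α/2, n−1)), where T is noncentral t with n−1 degrees of freedom and noncentrality d√n.

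- n = 45, d = 0.55, two-sided 0.05: noncentrality 0.55 × √45 = 3.69, critical value 2.015, power 0.950. The smallest n reaching 0.95 is 45.
- 30% loss: 45 / 0.70 = 64.3, rounded up to 65.

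Both figures reproduce. The stated power is thus power to detect a change from any cause.

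**When follow-up falls, for a woman screened in pregnancy.** Inputs from the Procedures section:

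- evaluation within one week of positive screening and the MINI within the following week: 0–2 weeks;
- a few weeks to form a group: 0–4 weeks (the number is assumed);
- ten weekly sessions: 10 weeks.

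T1 is therefore 10–16 weeks after screening, or later if the partner and mother–child sessions follow the ten. With term assumed at 40 weeks:

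- T1 is postnatal if screening is after week 40 − 16 = 24 to 40 − 10 = 30.
- T2 (26 weeks later) is postnatal if screening is after week 24 − 26 = −2 to 30 − 26 = 4, which is practically always.
- T3 (52 weeks later) has a threshold of −28 to −22, so it is always postnatal.

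The share of antenatal entrants whose T1 is postnatal depends on gestation at screening, which the protocol does not give. With uniform screening over weeks 4–40 it is 10/36 to 16/36, or 28–44%. Over weeks 12–40 it is 36–57%, over weeks 20–38 it is 44–78%, and over weeks 28–38 it is 80–100%.

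**What an untreated change would do.** Suppose the intervention does nothing and untreated women change by a standardized amount d. The documents give no such figure, so the range 0.2–0.55 is assumed. The same noncentral t formula gives the probability of a significant paired test:

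| Untreated d | n = 45, α = 0.05 | n = 45, α = 0.05/3 | n = 45, α = 0.05/6 | n = 22, α = 0.05 |
|---|---|---|---|---|
| 0.20 | 0.26 | 0.14 | 0.09 | 0.15 |
| 0.30 | 0.50 | 0.33 | 0.24 | 0.27 |
| 0.40 | 0.75 | 0.58 | 0.48 | 0.43 |
| 0.55 | 0.95 | 0.88 | 0.82 | 0.69 |

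The 0.05/3 column covers three comparisons with baseline, and the 0.05/6 column all pairs of four time points. The protocol does not say how many comparisons Bonferroni covers. The last column assumes that about half of the 45 completers (22) enrolled in pregnancy.

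**The case against.** The strongest reply is that the design is openly pre-post and the missing control group is listed as a limitation. Objective 4 sets out to evaluate and hypothesis 4 says only that the intervention can be effective, so neither announces a result. All of that is correct. But the limitation is general. It does not mention that baseline and outcome lie in different perinatal periods for antenatal entrants, and it does not alter the label in the Data Analysis Plan.

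Other objections succeed against stronger readings:

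- **That the protocol predicts improvement without treatment.** A reader might infer this from hypothesis 1 and from the Background's "Typically, this situation tends to resolve itself naturally". The Background sentence concerns ordinary mood variation and goes on to say that disorders can take hold or worsen. The treated women have a clinical diagnosis. Hypothesis 1 concerns prevalence; with a single screening per woman it compares largely different women and does not describe the course within one. The Data Analysis Plan's premise points the other way, so the direction of any bias is unsettled.
- **That most T1 scores are postnatal.** The share runs from 28% to 100% by assumption. Giving the infant temperament questionnaire at the end of the intervention hints at a postnatal T1 but does not establish it.
- **That 26–95% is the error rate of the antepartum claim.** Those figures use all 45 completers, no multiplicity correction and an assumed drift. Similar figures would apply to any single-arm study of this size, and the protocol states no rule for declaring effectiveness.

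**Conclusion.** The point holds in limited form. The Data Analysis Plan gives the name of treatment effect to an uncontrolled change and describes no separation of antenatal from postnatal entrants, while objective 4 and hypothesis 4 single out antepartum depression. For antenatal entrants, T2 and T3 are postnatal in practically every case, and T1 is postnatal when screening comes after about week 24–30. This rests on term at 40 weeks and 10–16 weeks from screening to T1. In these women d cannot be attributed to the intervention.

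The size of the distortion cannot be derived from the documents. For an assumed untreated d of 0.2–0.55, an ineffective intervention would give a significant test in 26–95% of studies (n = 45, unadjusted), 14–88% (n = 45, three Bonferroni comparisons) or about 15–69% (22 antenatal women, unadjusted). If the change at birth runs the other way, it would conceal benefit instead. The pre-post data remain usable as description; what is limited is the conclusion on objective 4.

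**What to change.** 1. In the Data Analysis Plan, replace the term treatment effect with standardized pre-post change.
2. In objective 4 and hypothesis 4, state that the change after the intervention is not separable from natural course.
3. Report the change separately for women enrolled antenatally and postnatally. For antenatal entrants, describe T1 by whether the woman was still pregnant or had delivered.
4. Present T2 and T3 as course over time.
5. Reconcile hypothesis 1 with the opening premise of the Data Analysis Plan on whether depression is more frequent before or after birth.

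The antepartum statement should not rest only on women still pregnant at T1. That would select those screened early, leave the natural course within pregnancy uncontrolled, and use a small part of the 45.

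The cost is wording and a descriptive split, with no new arm or visit. The protocol does not say outright that delivery dates are recorded for antenatal entrants. Infant age is needed to choose between the 1–12 and 12–36 month temperament scales, however, so delivery timing should be obtainable. The downside is a weaker claim and small, imprecise subgroups.

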#### Phase 5: Follow-up

Changes in the patients’ clinical conditions are re-evaluated at three points of follow-up (end of intervention, 6th month and 12th month) using EPDS, PHQ-9, STAI, WHOQOL-BREF, QUITs, MINI-Plus and a clinical interview.

Mothers who are still depressed after the intervention phase are sent to a clinical psychological or psychiatric service.

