### Study Outcomes

The data on maternal psychosocial and clinical conditions will be gathered. The primary outcomes are maternal depressive and anxiety symptoms severity. Secondary outcomes are maternal perceived quality of life and infants’ temperament (only for the infants whose mothers participated in the intervention).

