#### Italian Questionnaires of Temperament

The QUIT (Axia, 2002) is a set of questionnaires that are used to measure temperament in infants from the first month up to 11 years of age. This study uses the QUIT 1–12 and 12–36 month Scales. It is a caregiver-report questionnaire validated with reference to Italian culture, containing 55 items investigating six dimensions: attention, inhibition to novelty, motor activities, positive emotionality, negative emotionality and social orientation. The first three dimensions relate to adaptation in general, while the second three relate to specific adaptation to the social world. The answer to each item is on a six-point Likert scale with which mothers indicate their baby’s positive or negative attitude toward the environment, with higher scores indicating greater intensity of a characteristic. Four infant temperamental profiles can be obtained on the basis of the orthogonal dimensions of positive and negative emotionality: emotional temperament, calm temperament, normal temperament, difficult temperament. The QUIT has acceptable internal consistency with Cronbach’s alpha ranging from 0.59 to 0.71 (Axia, 2002), and the Pearson’s correlation coefficient among reports by mothers and fathers ranges from 0.32 to 0.62 (Axia and Weisner, 2002).

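### The treatment-effect analysis does not exempt infant temperament (QUIT), so change across infant ages and two age-specific forms would be labelled an effect of the mother's intervention

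*Protocol article*

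**What the plan says.** Under effectiveness of treatment, the Data Analysis Plan opens with "With regard to the effectiveness of treatment, standard descriptive statistics will be calculated for all questionnaires". A repeated-measures ANOVA is then to "compare the differences between each initial score obtained with the different administered questionnaires and the scores at T1", T2 and T3, with Bonferroni post hoc comparisons. Two further sentences follow, neither of which restricts the instruments: "Treatment effect will be calculated using Cohen’s d for each of the follow-up times" and "The Reliable Change Index will be calculated for each time, in order to determine any significant clinical changes occurring in each individual case post treatment".

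The QUIT is one of these instruments. Phase 3 (Psychodiagnostic Evaluation) gives it to mothers with a clinical diagnosis. Phase 5 repeats the assessment at all three follow-ups "using EPDS, PHQ-9, STAI, WHOQOL-BREF, QUITs, MINI-Plus and a clinical interview". Study Outcomes gives it formal status: "Secondary outcomes are maternal perceived quality of life and infants’ temperament (only for the infants whose mothers participated in the intervention". The QUIT section adds "This study uses the QUIT 1–12 and 12–36 month Scales".

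The article does not say how scores from the two forms are put on a common footing, and it states no age norm or age adjustment.

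**The concern.** For the maternal scales, a pre-post change has at least a clear meaning: the same instrument, in the same woman, on a symptom or quality-of-life score. For the QUIT, the infant's age changes substantially between visits and the instrument changes at 12 months. The ANOVA's null hypothesis is that mean scores are equal at every visit. That is a different statement from *the intervention does not affect temperament*, because scores can differ through development or through the change of form.

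If the plan is followed as worded, a difference of that kind would be reported as a treatment-effect Cohen's d, and for individual infants as clinical change after treatment. No untreated infants are measured, so nothing in the data could show how much of the change would have occurred anyway.

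This point concerns the effectiveness analysis only. It does not concern the separate objective on the influence of maternal mood on temperament.

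**Working it through.** **1. The plan's own figure.** Sample Size gives 45 patients for *d* = 0.55 on the EPDS, power 0.95, alpha 0.05, and 65 enrolled after 30% loss. A paired t test (noncentral t, two-sided 0.05) needs a minimum of n = 45, with power 0.950. For enrolment, 45 / 0.7 = 64.3, rounded up to 65. Both figures reproduce. They concern the EPDS and are not in question; 45 is used below as the largest planned analysed number.

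**2. Infant age at each visit, postnatal recruits.** Inputs: infant aged up to 6 months at entry (Inclusion Criteria); 10-week intervention and follow-up to 12 months after it (Procedures). Ten weeks = 10 / 52.18 × 12 = 2.3 months.

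| Visit | Formula | Age range (months) |
|---|---|---|
| Initial | entry age | 0 to 6 |
| T1 | entry + 2.3 | 2.3 to 8.3 |
| T2 | entry + 2.3 + 6 | 8.3 to 14.3 |
| T3 | entry + 2.3 + 12 | 14.3 to 20.3 |

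The two one-week assessment windows would add about half a month. The QUIT starts at the first month, so the lowest usable entry age is nearer 1 month. Every initial score is on the 1–12 month form and every T3 score on the 12–36 month form. At T2 the sample is split: infants older than 12 − 8.3 = 3.7 months at entry have already changed form.

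**3. Antenatal recruits.** No infant exists at the initial assessment. If the intervention starts 10, 20 or 30 weeks before birth (assumed values), T1 falls at 0, −2.3 or −4.6 months of age and T3 at 12.0, 9.7 or 7.4 months. Phase 4 places a QUIT before the mother–child module, but that is not an initial score. So the number of infants with a baseline QUIT is below the number of mothers analysed, by an amount the article does not give.

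**4. How often the ANOVA would be significant with no treatment effect.** The article gives no QUIT age trend, so drift and correlation are assumptions. Model: normal scores at four visits, equal correlation ρ between visits, mean = drift × (months since baseline) / 14.5 at 0, 2.5, 8.5 and 14.5 months (ten weeks rounded up), Greenhouse–Geisser-corrected F test at 5%, 4,000 simulated trials per setting.

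| Drift, baseline to T3 | N = 45, ρ = 0.5 | N = 45, ρ = 0.3 | N = 20, ρ = 0.5 |
|---|---|---|---|
| 0.2 SD | 18% | 14% | 9% |
| 0.3 SD | 41% | 29% | 18% |
| 0.5 SD | 87% | 72% | 45% |

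With zero drift, N = 45 and ρ = 0.5 the rate is 4.5%, as it should be. N = 20 is an assumed illustration of fewer infants with a baseline score.

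**5. Analytic cross-check.** At ρ = 0.5 the SD of a change score is √(2(1 − 0.5)) = 1 SD, so drift in SD units is the paired effect size. The paired t test of T3 against initial at n = 45 is then significant with probability 0.26, 0.50 or 0.91 at 0.05 for drifts of 0.2, 0.3 or 0.5 SD. At the Bonferroni level 0.05/6 these become 0.09, 0.24 or 0.72.

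**6. Reliable Change Index.** Threshold = 1.96 × √(2(1 − reliability)) SD. With the QUIT alphas of 0.59 and 0.71 this is 1.77 SD and 1.49 SD. If all infants shifted by an assumed 0.5 SD, the share classed as reliably changed in that direction would rise from 2.5% to about 8–10%.

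**The case against.** The strongest reply has four parts.

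*Scoring is not stated.* The article never says that raw QUIT scores are analysed. Age-standardised scoring is the kind of detail an article leaves to the full protocol, and it would largely remove the drift. This stands: the point is conditional on scoring. It still needs an answer, because the analysis text specifies a contrast that crosses forms and says nothing on how to make them comparable.

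*The d and Reliable Change sentences do not name the QUIT.* The effectiveness objective and hypothesis concern depression, and power rests on the EPDS, so a maternal-only reading is possible. But the ANOVA sentence covers the different questionnaires, the next sentences exclude none, and temperament is a declared secondary outcome. If the narrower reading is intended, saying so is the fix.

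*The missing control group is already disclosed.* Strengths and Limitations does concede it. That general caveat does not mention infant maturation or a change of instrument during follow-up.

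*The simulated rejections are not test errors.* Correct: the means differ by construction and the ANOVA detects a real difference. The fault lies in the label attached to it.

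A reader might also infer that maturation is certain to appear as a treatment effect, that the sponsor would present it as benefit to infants, or that QUIT scores have no better or worse direction. The document supports none of these. It gives no age trend, no hypothesis predicts a temperament benefit, and the QUIT section includes a difficult-temperament profile, although it describes dimension scores only in terms of intensity.

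**Conclusion.** The point holds in a limited form. As worded, the effectiveness scheme includes the QUIT, and for every postnatal recruit who reaches T3 the T3-versus-initial contrast crosses two forms at two developmental stages. That follows from the protocol's own entry age, durations and form ranges. Antenatal recruits cannot contribute an initial score at all. Whether this distorts results depends on scoring that the article does not state, and by how much depends on a drift that it does not give. At N = 45 and an assumed correlation of 0.5, assumed drifts of 0.2 to 0.5 SD give significance rates of about 18% to 87% with no treatment effect; fewer infants with a baseline score would lower them. The primary outcomes and the sample size are not affected. The wording should be corrected before the QUIT is analysed.

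**What to change.** In the Data Analysis Plan, limit the pre-post effectiveness ANOVA, the treatment-effect Cohen's d and the Reliable Change Index to the maternal scales (EPDS, PHQ-9, STAI, WHOQOL-BREF). Report the QUIT descriptively by infant age and form. Make no raw-score contrast across forms. If change is analysed, use only scores standardised by age and form, and label the result change with age in treated dyads.

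An age covariate alone should not be offered as a remedy. Within an infant, age equals age at baseline plus elapsed time, so it cannot separate maturation from treatment.

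In Study Outcomes, state that the single-arm design gives no estimate of the intervention's effect on temperament.

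The cost is wording, plus the loss of a treatment-effect claim on one secondary outcome. Infant age is needed at each QUIT administration. The article does not say that it is recorded at each visit, but choosing the right form already requires it.

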### Measures

#### Edinburgh Postnatal Depression Scale

The EPDS (Cox et al., 1987) is the most widely used screening tool for depressive symptoms during the perinatal period (de Moraes et al., 2017; Ukatu et al., 2018). It is a self-rating scale containing 10 items about symptoms of depression such as anhedonia, feelings of guilt, lethargy, sleep disturbance and suicidal ideation. The answer to each item is on a four-point Likert scale with which mothers indicate the frequency with which they have experienced the corresponding symptom during the past 7 days. The total score ranges from 0 to 30, with higher scores indicating more severe depressive symptoms. The internal consistency of the Italian version of the EPDS (Cronbach standardized alpha) was 0.80 (Benvenuti et al., 1999), which is similar to the value reported by Cox in the first validation study (0.87). The sensitivity, specificity, and positive predictive value of the Italian version were recorded as 55.6, 98.9, and 90.9%, respectively, based on a cut-off score ≥12, making it a reliable and valid screening tool for perinatal depression. Furthermore, a recent study (Smith-Nielsen et al., 2018) found that a score of 11 or more is the optimal cut-off for depression according to both DSM-5 (American Psychiatric Association, 2013) and ICD-10 criteria (World Health Organization, 1992).

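### The Reliable Change Index, used with no end-state criterion, cannot by itself establish clinically significant change: a woman can pass it and still score above the EPDS cut-off

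*Protocol article*

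**What the plan says.** The Data Analysis Plan compares baseline with the end of treatment, 6 months and 12 months by repeated-measures ANOVA with Bonferroni comparisons, and gives Cohen's d at each follow-up. It then turns to individual women: "The Reliable Change Index will be calculated for each time, in order to determine any significant clinical changes". No second condition is attached to that sentence.

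The EPDS section under Measures supplies what an end-state condition would need. On the scale: "The total score ranges from 0 to 30, with higher scores indicating more severe depressive symptoms". On reliability: "The internal consistency of the Italian version of the EPDS (Cronbach standardized alpha) was 0.80", with 0.87 cited from the first validation study. Two cut-offs are cited. The accuracy figures for the Italian version are "based on a cut-off score ≥12", and a later study is cited as finding that "a score of 11 or more is the optimal cut-off for depression". The PHQ-9 and STAI sections also cite cut-offs (10 or more; 40 or more, and elsewhere above 40). All of these appear as properties of the instruments.

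Phase 5 (Follow-up) repeats the questionnaires, the MINI-Plus and a clinical interview at all three follow-ups, and identifies mothers who are still depressed after the intervention so that they can be referred. Nothing links that status to the conclusion about clinical change.

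**The concern.** Reliable change and clinically significant change answer different questions. The first asks whether the difference between two scores is larger than the instrument's error. The second asks whether the woman has reached a state that matters, and that depends on the final score or diagnosis. The plan names a method for the first question and states a conclusion that belongs to the second. This is more than detail left to a fuller document, because the article gives both the method and the inference to be drawn from it.

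The index is also the only individual-level effectiveness analysis named in the Data Analysis Plan. The limitations section acknowledges that there is no control or waiting-list group, so readers may lean on individual change rates when judging benefit. If those rates carry the label of clinical change, they can include women who still screen positive. The same woman could be recorded as still depressed at follow-up and reported as clinically changed.

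**Working it through.** **The plan's own figures.** The document gives no reliable-change threshold, so there is none to reproduce. The sample-size figures do reproduce. A two-sided paired t-test with d = 0.55, n = 45 and alpha 0.05 has power 0.9503, and 45 / 0.70 = 64.3, rounded up to 65. Neither depends on the index.

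**Inputs.** EPDS reliability r = 0.80 and 0.87, and cut-offs of 12 or more and 11 or more, all from the EPDS section. The document gives no EPDS SD, so SD = 3, 4, 5 and 6 are assumptions.

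**Formula.** RCI = (baseline − follow-up) / [SD × √(2(1 − r))]. A change is reliable at the usual 5% level when it exceeds 1.96 × SD × √(2(1 − r)).

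- r = 0.80: 1.96 × √0.40 = 1.2396 per SD point, so SD 5 gives 6.20.
- r = 0.87: 1.96 × √0.26 = 0.9994 per SD point, so each threshold lies just under a whole number.

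The lowest baseline from which a woman can improve reliably and stay positive is the cut-off plus the smallest reliable whole-point fall.

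| r | SD (assumed) | Threshold | Smallest reliable fall | Lowest baseline, still ≥12 | Lowest baseline, still ≥11 |
|---|---|---|---|---|---|
| 0.80 | 3 | 3.72 | 4 | 16 | 15 |
| 0.80 | 4 | 4.96 | 5 | 17 | 16 |
| 0.80 | 5 | 6.20 | 7 | 19 | 18 |
| 0.80 | 6 | 7.44 | 8 | 20 | 19 |
| 0.87 | 3 | 3.00 | 3 | 15 | 14 |
| 0.87 | 4 | 4.00 | 4 | 16 | 15 |
| 0.87 | 5 | 5.00 | 5 | 17 | 16 |
| 0.87 | 6 | 6.00 | 6 | 18 | 17 |

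**Example.** A fall from 24 to 16 is 8 points. It exceeds the largest threshold in the table (7.44), and 16 is above both cited cut-offs. The index therefore labels this woman clinically changed in every row. A fall from 22 to 15 (7 points) does the same in every row except r = 0.80 with SD 6.

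**Illustration of frequency.** Scores were simulated as normal, rounded to 0–30 and restricted to a baseline of 12 or more. All settings were assumed: mean baseline 14, 16 or 18 (before the restriction), SD 4 or 5, pre–post correlation 0.5, and mean change 0.55, 1.0 or 1.5 SD. Among women passing the index, 9% to 74% still scored 12 or more (23% to 74% at a mean change of 0.55 SD), and 13% to 82% still scored 11 or more. The width of these ranges shows how far the answer depends on inputs the document does not supply.

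**The case against.** The best defence is that this is a matter of wording. The sentence speaks of changes, not recovery or remission. It does not define responders, promise a success rate or say that the index is the sole criterion. A woman who falls from 24 to 16 has changed. Diagnostic status is collected at every follow-up, and a fuller document could tabulate it. The primary outcomes are symptom severity, analysed at group level. Much of this stands and keeps the point small. It does not remove it, because the stated purpose of the index is to determine *clinical* change, and no other part of the protocol supplies the missing condition.

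A cut-off is also an imperfect end state. At 12 or more the protocol cites a sensitivity of 55.6%, so a lower score does not show that depression is absent. Women enter the intervention by diagnosis of depression and/or anxiety, so some may start below the EPDS cut-off. Both objections are fair, and the fix has to allow for them.

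Two stronger readings are tempting, and the document supports neither.

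- A reader might infer that the rule errs in both directions, because a fall from 14 to 8 crosses the cut-off yet fails the index at SD 5 and r = 0.80 (6 points against 6.20). A rule requiring reliable change *and* an end state below the cut-off would not count her either. At SD 4 (4.96), or at SD 5 with r = 0.87 (5.00), she passes the index.
- A reader might infer that a known share of women *will* be mislabelled. Without a documented SD or baseline mean, one can say only that some *can* be.

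**Conclusion.** The point holds as a minor one. The plan draws from the Reliable Change Index a conclusion about clinical significance that the index cannot support alone. On the EPDS, any woman with a baseline of at least 15 to 20 (cut-off 12) can meet the index and still screen positive. That range rests on the two reliabilities the protocol cites, an assumed SD of 3 to 6 and the conventional 1.96 criterion. The number of women affected cannot be stated, and the simulated shares are illustrations only. The repeated-measures ANOVA, Cohen's d and the sample size of 45 (65 enrolled) are untouched.

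**What to change.** In the Data Analysis Plan:

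- Describe the index alone as reliable change (improvement or deterioration).
- Report clinically significant change separately, in one of two ways. Either require reliable improvement plus a follow-up score below one pre-specified cut-off, among women who started at or above it, or use MINI-Plus non-case status at that follow-up.
- Name a single EPDS cut-off, since 12 and 11 are both cited. Do the same for any other scale used this way; the STAI text gives both 40 or more and above 40.
- Say how women who start below the cut-off are reported. The MINI-Plus module in use covers depressive disorders, so it cannot serve as the end state for women treated for anxiety alone.
- When results are reported, give the reliability and SD behind the index, because the threshold roughly doubles across the range above.

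The cost is a few lines of text and one extra table. Every item is already collected at each follow-up. The drawback is that the reported rate of clinical change will usually be lower than the rate of reliable change.
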